#### 2.5.3. Anthropometric and Physical Fitness Assessments

A series of anthropometric and physical fitness assessments are performed, following Standard Operating Procedure Forms (e.g., China National Physical Health Standards for Young Children (3–6 years old) and China National Physical Health Standards for Students-2014 Revision (≥7 years)), on all the participants at each assessment wave. All assessments are carried out by trained research staff members. Before each measurement, the instruments will be recalibrated.

*(1) Anthropometric Assessments*. Height and weight are measured twice and recorded to the nearest 0.1 cm and 0.1 kg, using a wall-fixed measuring device and an electronic platform scale, respectively. The results are used to calculate body mass index (BMI, kg/m^2^). Chest, waist, and hip circumferences are measured twice, all recorded to the nearest 0.1 cm, using a flexible tape. Skinfold thickness is measured twice and recorded to the nearest 0.1 mm by means of a skinfold caliper [41]. The following sites are used for skinfold thickness: biceps, triceps, subscapularis, and suprailiac. Grip strength is measured twice and recorded to the nearest 0.1 kg, using a hand-held dynamometer. Explosive strength of the legs and flexibility are also assessed via horizontal jump test and sit-and-reach test, respectively.

*(2) Agility*. Agility is assessed on a flat surface using the 10 m shuttle run test [42, 43]. Participants perform a 5 min warm-up that includes both stretching and jogging before the test. During each testing session, participants sprint 10 m, stop, and turn around and then sprint back to the starting line immediately. Participants are instructed to perform the test as fast as possible and change direction by pushing off the ankle. For the test, time starts at the “go” command and stops when the participant crosses back the starting line. The elapsed time is recorded using a stopwatch to the nearest 0.01 s. Each participant performs two trials in each test separated by 5 min rest interval.

*(3) Aerobic Fitness*. Aerobic fitness is assessed using the multistage 20 m shuttle run test, which has been widely used in previous studies of preschool children, adolescents, and young adults (20 m SRT) [44, 45]. Participants perform a 10 min warm-up that includes both stretching and jogging before the test. During each testing session, participant performs shuttle runs between two parallel lines (20 m apart) on a flat surface at initial speed of 8.5 km/h. The running speed increases by 0.5 km/h each minute, which is described as a change in test level. The running pace is determined by a sound signal emitted from a prerecorded audiocassette tape. When the participant can no longer maintain the prescribed pace for two consecutive signals or stops because of exhaustion, then the test ends. The participant's maximal oxygen uptake (VO_2_ max) is predicted using the recorded last level number.

#### 2.5.4. Measurement of IGF-1 and BDNF

After overnight fasting, venous blood samples are taken from participants following gained consent for attaining blood sampling components. All blood samples are collected between 7:00 and 8:00 am to minimize the effects of diurnal variation of plasma BDNF levels [46]. Breakfast is prepared under the guidance of the nutritionists to ensure good compliance. Two nurses perform the blood sampling from cubital veins using EDTA-coated tubes. Blood samples are immediately placed on ice and then centrifuged at 3500 rpm for 15 min in a 4°C centrifuge. Plasma samples are collected and stored at −80°C before the measurement. The plasma IGF-1 and BDNF concentrations are measured in duplicate using Enzyme-linked Immunosorbent Assay (ELISA) kits (for the first assessment wave, Human IGF-1 Quantikine ELISA kit and Human BDNF Quantikine ELISA kit, R&D Systems, USA), according to the manufacturer's instructions.

#### 2.5.5. Retrospective Questionnaire

Retrospective questionnaires are to be completed by all participants and their parents or legal guardians at each assessment wave. For the parents or legal guardians, data on family, educational level, occupation, household income, and lifestyle are collected. For the participants, data on behavior, diet, well-being, stress, and networks are collected. The data collected will be analyzed as potential covariates and moderators of the associations between physical activity and cognitive development. Additionally, 7-day physical activity recall data on the participant are collected because they can provide the information on water-based activity and bicycling ActiGraph's GT3X accelerometer cannot. The questionnaire can be completed in approximately 20 min with assistance from research staff member.

### 2.6. Statistical Analyses

All of the collected data are typed into EpiData 3.1 software (EpiData Association, Odense, Denmark), double-checked by two research staff members, and exported to SPSS version 22.0 (IBM Corporation, USA) for further analyses. Descriptive statistics are used to present baseline data and the following assessment waves as mean ± SD and median (interquartile ratio, IQR) for normally distributed and nonnormally distributed data, respectively. Prior to analyses, the log and square root methods are used for nonnormally distributed data. Linear regression models are performed to examine the relation of physical activity and cognitive development over time in more detail, with LPA, MPA, VPA, MVPA, and TPA assessed by ActiGraph's GT3X accelerometers as the independent variables, Verbal IQ, Performance IQ, and Full Scale IQ as dependent variables, and data collected by retrospective questionnaires and anthropometric and physical fitness assessments as covariates or moderators [47]. Exploratory analyses are also performed in order to examine whether plasma IGF-1 and BDNF concentrations serve as the mediators for the potential positive effects of physical activity on cognitive development [48].

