## Abstract

The aim of the study is to investigate the relationship between physical activity as assessed by accelerometers and cognitive development across the human age ranges (from children and adolescents to adults). Additionally, this study seeks to explore whether physical activity contributes to cognitive development via modification of plasma insulin-like growth factor 1 (IGF-1) and brain-derived neurotrophic factor (BDNF). In the study, 500 preschool children (3.5–5.5 years old) are taking part in 6 triennial assessment waves over the span of 15 years. At each wave, participant measures included (a) 7-day physical activity monitoring using ActiGraph's GT3X accelerometers, (b) the evaluation of cognitive development, (c) anthropometric and physical fitness assessments, (d) plasma IGF-1 and BDNF concentrations, and (e) retrospective questionnaires. Linear regression models are used to examine the effect of physical activity on cognitive development; plasma IGF-1 and BDNF concentrations are considered as mediators into data analyses. The results of the study may help to inform future health interventions that utilize physical activity as a means to improve cognitive development in children, adolescents, and adults. Additionally, the study may assist in determining whether the putative effects occur via modification of plasma IGF-1 or BDNF concentrations.

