## 2. Methods

### 2.1. Research Design

The PACD study uses a long-term, longitudinal, cohort design. In the present study, 500 preschool children (3.5 to 5.5 years old) are taking part in 6 triennial assessment waves across 15 years.

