### 2.3. Participants

The participants were 500 preschool boys (*n* = 250) and girls (*n* = 250) living in urban areas of Shanghai, China. Participants were made eligible for the study after screening done via a questionnaire and a health assessment. Children were recruited from 8–10 kindergartens, based on the following inclusion criteria: (1) child is in the 2nd grade in kindergarten; (2) both child and parent/legal guardian are able to speak Mandarin; (3) informed consent is signed by the parent/legal guardian of the child. Conversely, exclusion criteria for the participants include the following: (1) health issues that limit physical activity; (2) mental illness; and (3) participation in special education programs [12]. The inclusion and exclusion criteria were assessed by two trained research staff members and doctors from the kindergartens and Xinhua Hospital affiliated to Shanghai Jiao Tong University School of Medicine. The anticipated gender breakdown is expected to be 50% male and 50% female.

Children Physical Health Research Base (CPHRB) in kindergartens was constructed before the study. Participants were recruited through a parents' information evening in the targeted kindergartens. Rewards for participants will be printed reports of the results of Intelligence Quotient (IQ) scores, physical fitness, anthropometric assessments, and so forth. If parental or legal guardian consent is given at recruitment, blood sampling is done and the printed reports for the results of blood trace element contents are provided. After the first assessment wave, both the family members of the participants who complete the assessments and the kindergarten teachers are provided with free assessment services of physical fitness.

Tracking plans are made for maintaining contact between family members of participants and the researchers, thus maximizing retention of participants. This has to be done due to the long-term period for data collection [24]. The longitudinal tracking plan includes (1) obtaining home and cell phone numbers and e-mail addresses; (2) establishing WeChat group and QQ group which have all the parents or legal guardians of participants; (3) providing all the participants and their family members with free assessment service for physical fitness annually; and (4) awarding certificates for recognizing their contribution to the longitudinal research [25].

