### 2.5. Assessments

#### 2.5.1. Physical Activity Levels

Objective data of physical activity, including sedentary behavior (SB), light physical activity (LPA), moderate physical activity (MPA), vigorous physical activity (VPA), moderate-to-vigorous physical activity (MVPA), and total physical activity (TPA), are collected using accelerometers (GT3X, ActiGraph, Pensacola, FL). ActiGraph's GT3X accelerometers have been widely used in previous studies with preschoolers [27], children [28], and adolescents [29]. Except during water-based activities or while sleeping, the device is always worn on an adjustable belt positioned above the right hip.

During the first assessment wave, each accelerometer is set to collect physical activity data in counts units for each 1 sec epoch [30]. Cut-points for SB (<100 counts/min, cpm), MPA (≥1680 cpm), and VPA (≥3368 cpm) are consistent with previous related studies [31–33]. Floating Window algorithms will be used to define non-wear-time periods [34]. Each participant is instructed to wear the device for 7 consecutive days (including 5 weekdays and 2 weekend days). Participants with fewer than 3 days (2 weekdays and 1 weekend day) of valid accelerometer data (≥8 h per day) will be asked to redo the data collection wave.

To improve data correctness and completeness, research staff members will check the accelerometers worn by children every weekday morning in the kindergartens during the first assessment wave to ensure that they are functioning appropriately. Research staff members will also contact participant's parent or legal guardians every night using WeChat on cell phone during the 7-day monitoring period to ensure compliance and solve technical issues. Some teachers in primary and middle schools will be invited to join in the research group in order to help with checking the accelerometers during the following 5 assessment waves. This is because compliance monitoring may be difficult for research staff members due to the fact that the participants may be in many different schools.

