## 3. Results

The aim of this study is to describe the protocol of the PACD study. Prior to the first assessment wave, the procedures were pilot-tested for feasibility and user acceptability in a sample of 36 preschool children. At the pilot component of the study, valid accelerometer data were collected from 86.1% of children, anthropometric and physical fitness assessments were performed in 88.9% of children, venous blood samples were taken from 66.7% of children after consents were obtained for attending blood sampling, and questionnaires were completed by 94.4% of children and parent/legal guardian pairs. In addition, full C-WYCSI assessments were performed in 86.1% of children. Pearson's correlation detected that Full Scale IQ scores from short form of C-WYCSI assessments (including 4 subsets) had significantly positive correlations with those of full C-WYCSI assessments (*n* = 31; *r* = 0.90; *P* < 0.01). During the pilot study, two informed consents were withdrawn by the parents of the children. None of the accelerometers were lost, stolen, or broken. Valid data collected from the pilot study will be merged in the first assessment wave of the PACD study.

To date, 8 CPHRBs of kindergartens for the study have been established in Shanghai, China. Two more kindergartens will also be recruited into the PACD study. Participant recruitment and data collection for the first assessment wave are currently ongoing. A total of 346 children (57.5% male and 42.5% female) from the 7 kindergartens have been enrolled.

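### Section 2.6 names only linear regression for the over-time question, leaving repeated measures on a child and kindergarten clustering out of the model

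*Protocol article*

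**What the plan says.** Section 2.1 describes the design: "The PACD study uses a long-term, longitudinal, cohort design", in which "500 preschool children (3.5 to 5.5 years old) are taking part in 6 triennial assessment waves across 15 years". Section 2.3 gives the recruitment units: "Children were recruited from 8–10 kindergartens". The Results section reports progress: "A total of 346 children (57.5% male and 42.5% female) from the 7 kindergartens have been enrolled".

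For the analysis, section 2.6 says "Linear regression models are performed to examine the relation of physical activity and cognitive development over time in more detail". The exposures are five accelerometer measures of activity, and the outcomes are the three IQ scores. The covariates or moderators come from the questionnaires and from the anthropometric and fitness tests. The Abstract names the same model: "Linear regression models are used to examine the effect of physical activity on cognitive development".

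The article mentions no child effect, kindergarten term, correlation structure or cluster-robust variance. It also does not say whether the waves are stacked in one model, analysed one at a time, or linked by regressing later IQ on earlier activity.

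**The concern.** Linear regression in its usual sense assumes independent errors. The design breaks this at two levels: a child contributes up to six records, and children enter in blocks of about 50 per kindergarten. Positive correlation within a child is credible from the article itself, since the Introduction cites evidence that early cognitive scores relate to later mental ability.

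Two things are at stake. The first is the validity of standard errors and P values for the main aim. The second is what the coefficient means. A pooled regression blends differences between more and less active children with change in a child who becomes more or less active. The article justifies the study by the need for longitudinal evidence, so a reader needs to see these two apart.

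**Working it through.** The documents give no significance level, within-child correlation, intracluster correlation (ICC) or sample-size calculation, so there is no stated figure to reproduce. A two-sided 5% level and all correlations below are assumptions.

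**Inputs from the documents**
- 500 children and 6 waves (section 2.1): up to 500 × 6 = 3000 records.
- 8–10 kindergartens (section 2.3): 500/10 = 50 to 500/8 = 62.5 children each. Enrolment so far gives 346/7 = 49.4 (Results).

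**Formulas.** When records in units of size m are treated as independent, the variance of the slope is understated by the factor DE = 1 + (m − 1) × ρ_IQ × ρ_activity. The true error is 2 × [1 − Φ(1.96/√DE)].

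**Reading A: six waves pooled, within-child correlation only (m = 6)**

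| ρ_IQ | ρ_activity | DE | True error |
|---|---|---|---|
| 0.7 | 0 | 1.00 | 5.0% |
| 0.5 | 0.1 | 1 + 5 × 0.05 = 1.25 | 8.0% |
| 0.8 | 0.1 | 1 + 5 × 0.08 = 1.40 | 9.8% |
| 0.7 | 0.3 | 1 + 5 × 0.21 = 2.05 | 17.1% |
| 0.5 | 0.5 | 1 + 5 × 0.25 = 2.25 | 19.1% |
| 0.8 | 0.5 | 1 + 5 × 0.40 = 3.00 | 25.8% |

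At 0.7/0.3 the 3000 records carry the information of 3000/2.05, about 1460 independent ones, and correct standard errors are √2.05 = 1.43 times the naive ones. A null simulation (3000 replicates, 500 children, 6 waves) gave 17.4% at 0.7/0.3, 24.0% at 0.7/0.5 and 8.2% at 0.6/0.1, in line with the formula.

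**Reading B: one record per child, kindergarten clustering only (m = 50 or 62.5)**

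| ICC IQ | ICC activity | DE | True error |
|---|---|---|---|
| 0.01 | 0.05 | 1.02–1.03 | 5.3–5.4% |
| 0.05 | 0.10 | 1.25–1.31 | 7.9–8.7% |
| 0.10 | 0.10 | 1.49–1.62 | 10.8–12.3% |

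Simulated single-wave values were slightly lower: 6.8% at 0.05/0.10 with 10 kindergartens, and 11.1% at 0.10/0.10 with 8.

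**Both levels, waves pooled.** If kindergarten effects persist through all six waves, simulation gave 9.1% at low correlations (0.5/0.1, ICCs 0.01/0.05) and 28.2% at 0.7/0.3 with ICCs 0.05/0.10. Section 2.5.1 notes that after the first wave "the participants may be in many different schools", so these combined figures lean high and the conclusion does not rest on them.

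**Change over time under Reading B.** The Introduction asks whether the association is confined to certain ages, present throughout, or changing. Coefficients from separate wave models come from the same children and are therefore correlated. Testing whether they differ needs their covariance, which separate regressions do not supply.

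**The case against.** The strongest reply is that pooling is an inference. Section 2.6 speaks of models in the plural and does not say that six records per child are stacked as independent. Wave-by-wave regressions, or later IQ on earlier activity, fit the wording too, and they leave only kindergarten clustering. This stands. A reader might infer that the plan commits to a false-positive rate several times 5%. The documents do not support that, because they fix neither the pooling nor any correlation. With weak tracking of activity (0.1), even the pooled error stays below twice 5%.

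Other points also stand:
- The calculation assumes one constant correlation, six complete waves and no covariates. Section 2.5.2 has three instruments over 15 years, and the socioeconomic covariates in section 2.5.5 could absorb part of the correlation.
- The direction is not universal. For purely within-child contrasts, naive standard errors can be too large.
- Wave-specific models do speak to whether an association exists at particular ages.
- The article names no within-child estimand, so that coefficient should be reported beside the between-child one, not in its place.

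It can also be said that an article leaves correlation structure to a fuller plan. That would answer a silent article. This one names the model for its main aim, in both the Abstract and section 2.6, and the named model does not fit the design. No reading of section 2.6 brings in kindergarten.

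**Conclusion.** The point holds in conditional form. The stated method accounts for neither level of dependence in the design.

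- **If waves are pooled as independent records**, standard errors for the activity–IQ association are too small whenever both variables track within child. The true error is about 8–26% for ρ_IQ 0.5–0.8 and ρ_activity 0.1–0.5, and 5% if activity does not track.
- **If each wave is analysed alone**, the error from kindergarten clustering runs from about 5% at very small ICCs, through 8–9% at 0.05/0.10, to 11–12% at 0.10/0.10. The question of change over time in the same children is left untested.

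These are ranges under assumed correlations, not properties of the protocol. The mismatch between model and design does not depend on them.

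**What to change.** In section 2.6, replace linear regression for the over-time question with a linear mixed model fitted by maximum likelihood, so that children with missed waves stay in. Include:
- a random intercept per child, and a random age slope if it can be estimated;
- age or wave;
- kindergarten of enrolment as fixed effects, since 8–10 units are too few for a dependable random effect;
- activity as two terms, the child's own mean across waves and the wave-specific deviation from it, with both coefficients reported.

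Kindergarten is constant within a child, so its fixed effects protect the between-child coefficient and add essentially nothing to the within-child one. For any single-wave analysis, include kindergarten as fixed effects. Such a model targets the nominal error rate by construction; this was not simulated.

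The cost is a rewording of section 2.6, wider intervals for between-child associations, and 7–9 degrees of freedom for 8–10 kindergartens. No new data are needed, and at the time of the article the first wave was still recruiting.

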## 3. Results

The aim of this study is to describe the protocol of the PACD study. Prior to the first assessment wave, the procedures were pilot-tested for feasibility and user acceptability in a sample of 36 preschool children. At the pilot component of the study, valid accelerometer data were collected from 86.1% of children, anthropometric and physical fitness assessments were performed in 88.9% of children, venous blood samples were taken from 66.7% of children after consents were obtained for attending blood sampling, and questionnaires were completed by 94.4% of children and parent/legal guardian pairs. In addition, full C-WYCSI assessments were performed in 86.1% of children. Pearson's correlation detected that Full Scale IQ scores from short form of C-WYCSI assessments (including 4 subsets) had significantly positive correlations with those of full C-WYCSI assessments (*n* = 31; *r* = 0.90; *P* < 0.01). During the pilot study, two informed consents were withdrawn by the parents of the children. None of the accelerometers were lost, stolen, or broken. Valid data collected from the pilot study will be merged in the first assessment wave of the PACD study.

To date, 8 CPHRBs of kindergartens for the study have been established in Shanghai, China. Two more kindergartens will also be recruited into the PACD study. Participant recruitment and data collection for the first assessment wave are currently ongoing. A total of 346 children (57.5% male and 42.5% female) from the 7 kindergartens have been enrolled.

## 4. Discussion

As discussed above, the accumulated evidence demonstrates that physical activity is positively associated with cognitive function and academic performance in early life [7–9]. However, stronger, more compelling evidence from longitudinal studies is still required. A systematic review of three databases of literature (SPORTDiscus, ERIC, and PubMed) from 2000 to 2013 found only three longitudinal studies done on adolescents [9]. This review reported a lack of longitudinal studies that included children's age. To address this limitation, the PACD study is designed to test whether the putative effects of physical activity on cognitive development are present from early childhood to adulthood.

In recent years, studies of the effect of physical activity on cognitive development are moving from descriptions of the relationship to in-depth explorations of the mechanisms [49–51]. The PACD study also seeks to investigate the possible role of plasma IGF-1 and BDNF in mediating activity-related cognitive development. Overall, pilot study results generally support the feasibility and acceptability of the methods and measures. However, a few modifications of the study protocol have been made to reduce participant burden and improve compliance and data quality.

At the pilot component of the study, the full C-WYCSI assessment (including 11 subsets) lasted approximately 1 h and 45 min for each child. This time frame was determined to be too arduous for the preschool children. The results of pilot study showed that Full Scale IQ scores from short form of C-WYCSI assessments were significantly correlated with those from full C-WYCSI assessments. As an alternative approach, the short form of C-WYCSI assessment lasted for 40 min for each child, which resulted in improved compliance. To reduce the stress of a lengthy assessment of the participants, the short form of C-WYCSI is used at the first assessment wave.

To administer the shuttle run tests, two parallel lines were marked (10 or 20 m apart) on a flat surface, using 2 separate pieces of tape. The preschool children were instructed to touch the tape before they turn back at the pilot component of the first assessment wave. However, most of the preschool children found it difficult to stop and run back immediately after touching the tape. Interestingly enough, the tests for preschool children were completed better when we asked them to use their hand to touch the box set on the tape instead of touching the tape directly. The alternative approach will be used at the first two assessment waves.

The pilot component of the study found that all the preschool children were unable to coordinate and maintain their running speed with the prescribed pace just following sound signals from the audiocassette tape, during the 20 m SRT. To address the feasibility of test, two research staff members were trained to perform the tests with the children. During each testing session, the children were asked to run in synchrony with the research staff member. This approach will be used at the first three assessment waves.

To date, the standard operating procedures have been established for the first assessment wave through the pilot study. More pilot studies will be carefully conducted before the following assessment waves. Dissemination of the PACD study includes presentations at research conferences and papers published in peer-reviewed journals.
